#### **11.6. Urgent Safety Measures**

The Chief Investigator may take urgent safety measures to ensure the safety and protection of the clinical trial patients from any immediate hazard to their health and safety. The measures should be taken immediately. In this instance, the approval of the REC prior to implementing these safety measures is not required. However, it is the responsibility of the Chief Investigator to inform the Sponsor and REC (via telephone) of this event immediately.

The Chief Investigator has an obligation to inform the REC in writing within 3 days, in the form of a substantial amendment. The Sponsor (Joint Research Management Office [JRMO]) must be sent a copy of the correspondence.

#### **11.7. Annual Safety Reporting**

The Chief Investigator will send an Annual Progress Report to the main REC using their template (the anniversary date is the date on the REC "favourable opinion" letter from the REC) and to the Sponsor.

#### **11.8. Overview of the Safety Reporting responsibilities**

The Chief Investigator has the overall safety oversight responsibility. The Chief Investigator has a duty to ensure that safety monitoring and reporting is conducted in accordance with the Sponsor's requirements.

## **12. Statistical Considerations**

### **12.1. Power calculations and sample size determination**

1684 participants are to be recruited from 15-25 centres allocated in a ratio of 1:1.

The sample-size calculation is based on a prevalence of new onset AF in the tight potassium control arm of 35%, which is at the lower end of the published figures and supported by our pilot data that showed an overall prevalence of 36.8% (95% confidence interval [CI] 29.1 to 44.9).

The co-applicants (from diverse backgrounds in cardiothoracic surgery, cardiothoracic intensive care, cardiology and clinical trial management) reached consensus that that a clinically relevant non-inferiority margin is 10%. If there is a true difference in favour of tight potassium control of 2%, then 1514 participants are required to be 90% certain that the upper limit of a one-sided 97.5% CI (or equivalently a 95% two-sided CI) will exclude a difference in favour of tight potassium control of more than 10%. Allowing for a 10% loss to follow-up means we need to recruit 1684 participants.

#### **12.1.1. Tight K Australia**

The Tight K Trial (UK) is a collaboration with a partner trial in Australia (also called Tight K), which will recruit 550 participants. The UK trial is sufficiently powered on its own. The data from both trials will form a prospective meta-analysis, providing further power and aiding generalisability.

### **12.2. Trial statistician**

Statistical analysis will be coordinated from the CTU at LSHTM.

### **12.3. Statistical analysis**

Statistical analysis will be carried out blind to treatment allocation.

#### **12.3.1. Summary of baseline data and flow of participants**

Baseline characteristics of enrolled participants will be summarised by treatment arm. Descriptive statistics for continuous variables will include mean, standard deviation, median, range and number of observations. Categorical variables will be summarised as counts and proportions. Screening, enrolment, reasons for non-enrolment, randomisation and loss to follow-up will be detailed in a CONSORT flowchart.

#### **12.3.2. Primary and secondary outcome analyses**

As this is a non-inferiority trial, the primary and secondary outcome analyses will be carried out on the per-protocol population. An intention-to-treat (ITT) analysis will also be carried out. Analysis will follow a pre-specified analysis plan approved by the senior statistician and Chief Investigator prior to unblinding the study database. The criterion for statistical significance at the final analysis will be  $P < 0.05$ . The rate of loss to follow-up will be reported. We will report risk ratios for prevalence of new onset AF hour 120 after surgery or discharge from hospital (primary outcome) and for inpatient and six month mortality after enrolment

(secondary outcomes) for intervention versus control with associated 95% CI. Secondary outcomes: length of ICU and length of hospital stay, will be analysed using Kaplan-Meier plots and the hazard ratios with accompanying 95% CI calculated using Cox proportional hazards regression. All other secondary outcomes will be analysed using appropriate regression models accounting for the nature of the distribution of the outcome and results will be presented as appropriate effect sizes with a measure of precision (95% CI). Both unadjusted analyses and analyses adjusted for the stratification factor will be carried out. Additional exploratory analyses will control for any baseline measures that appear to be imbalanced between arms.

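### The non-inferiority margin and sample size are on the absolute risk-difference scale, but the analysis section names only a risk ratio and never links it to the 10-point margin

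*Protocol*

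**What the plan says.** Protocol section 12.1 assumes a "prevalence of new onset AF in the tight potassium control arm of 35"%, a figure it regards as "supported by our pilot data that showed an overall prevalence of 36.8"% (95% CI 29.1 to 44.9). It records a consensus that "a clinically relevant non-inferiority margin is 10"%. The calculation allows for relaxed control being slightly worse, by 2%, and asks for 1514 evaluable participants to give 90% power at a one-sided 97.5% confidence level. The requirement placed on the upper confidence limit is that it "will exclude a difference in favour of tight potassium control of more than 10"%. The section treats this limit as equivalent to that of a two-sided 95% interval. Adding 10% for loss to follow-up gives 1684. The word absolute does not appear beside the 10% or the 2%.

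Section 12.3.2 opens by recalling that this is a non-inferiority trial and refers to an analysis plan to be approved before unblinding. It then fixes two things itself. The effect measure: "We will report risk ratios for prevalence of new onset AF hour 120 after surgery or discharge from hospital (primary outcome"), with a 95% CI; the same sentence covers in-patient and six-month mortality. The criterion: "The criterion for statistical significance at the final analysis will be" P < 0.05. It does not mention a risk difference, the 10% margin, a margin on the ratio scale, or how an interval is to be compared with a margin.

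**The concern.** A non-inferiority conclusion needs an estimate, an interval and a margin on the same scale. Section 12.1 supplies the margin and the interval level for a difference. Section 12.3.2 supplies an estimate and interval for a ratio, and a P-value threshold with no null value. A risk ratio with its interval does not by itself settle whether the absolute excess is below 10 points, because the ratio equivalent to 10 points moves with the control-arm risk.

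Two things are at stake. If the ratio is judged against a converted margin, the power is not the one the trial was sized for, and the error rate at a true 10-point excess depends on the AF prevalence. If P < 0.05 is taken as a test of no difference, it answers a different question from the one the trial asks, and the two sections can lead to opposite headlines from the same data.

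**Working it through.** **Inputs** (all from section 12.1): control risk 35%; true difference 2 points, so 37% with relaxed control; margin 10 points; one-sided 2.5%; power 90%; 1:1 allocation; 10% loss. The pilot interval, 29.1% to 44.9%, serves below as a plausible range for control risk. This is an assumption, since it describes overall pilot prevalence.

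**1. Reproduce the sample size on the difference scale.**

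n per arm = (1.960 + 1.2816)² × (0.35×0.65 + 0.37×0.63) / (0.10 − 0.02)² = 10.507 × 0.4606 / 0.0064 = 756.2, so 757 per arm and 1514 in total. Then 757 / 0.9 = 841.1, so 842 per arm and 1684 in total. Both figures match exactly.

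**2. Try other readings of the design.**

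| Reading | Total evaluable |
|---|---|
| Absolute 10 points, one-sided 2.5% | 1514 |
| Same, one-sided 5% | 1234 |
| Same, no true difference | 958 |
| Margin 10% relative (3.5 points) | 43,020 |
| Risk-ratio margin 1.10, log scale | 47,370 |
| Risk-ratio margin 45/35 = 1.286, log scale | 1954 |

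Of these, only the absolute difference at one-sided 2.5% gives 1514.

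**3. Convert the margin to a risk ratio.** RR = (p + 0.10) / p, where p is the control risk:

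- 29.1%: 0.391 / 0.291 = 1.344
- 35%: 0.45 / 0.35 = 1.286
- 36.8%: 0.468 / 0.368 = 1.272
- 44.9%: 0.549 / 0.449 = 1.223

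**4. Power if the risk ratio is judged against 1.286** (757 per arm, 37% v 35%).

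SE of log RR = √[(0.65/0.35 + 0.63/0.37) / 757] = √(3.560 / 757) = 0.0686. Distance to the margin = ln(1.286) − ln(0.37/0.35) = 0.2513 − 0.0556 = 0.1957. Power = Φ(0.1957/0.0686 − 1.960) = Φ(0.894) = 81.4%.

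On the difference scale: SE = √(0.4606 / 757) = 0.0247, and power = Φ(0.08/0.0247 − 1.960) = 90.0%.

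The same formulas across the pilot range:

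| Control risk | Power, difference rule (true +2 points) | Power, RR 1.286 rule (true +2 points) | Chance the RR 1.286 rule declares non-inferiority at a true +10 points |
|---|---|---|---|
| 29.1% | 92.4% | 65.5% | 0.5% |
| 35% | 90.0% | 81.4% | 2.5% |
| 44.9% | 87.8% | 96.1% | 16.0% |

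The intended value in the last column is 2.5%.

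**5. One possible result read under each rule.** Suppose 40% v 35% is observed with 757 per arm.

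- Difference: 5.0 points, SE = √[(0.40×0.60 + 0.35×0.65) / 757] = 0.02485, 95% CI 0.1 to 9.9 points. The upper limit is below 10, so relaxed control is non-inferior under section 12.1.
- Test of no difference: 0.05 / 0.02485 = 2.01, P about 0.044, which would be read as significantly more AF.
- Ratio: 0.40/0.35 = 1.14, 95% CI 1.003 to 1.302. The upper limit exceeds 1.286, so a converted-margin rule would not declare non-inferiority.

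**The case against.** The strongest reply is that the rule already exists. Section 12.1 states the margin and the interval level, nothing in section 12.3.2 withdraws them, and the risk difference comes from the same two-by-two counts as the ratio. Saying that risk ratios will be reported does not exclude a risk difference or make the ratio the decision statistic. This stands in part: the fault is one of specification, not of design or data. But the usable rule appears only as a sizing assumption, while the section that governs the analysis names another measure and another criterion.

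A second reply is that the analysis plan, which is not shown, may settle the matter. It may. Even so, section 12.3.2 does not simply leave the measure and criterion open; it states both, and they do not fit section 12.1. A plan that makes the risk difference decisive would need protocol text that supports it.

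A reader might go further and infer three things that the protocol does not support:

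- **That the trial cannot test its hypothesis.** It can: the data will give the risk difference, and section 12.1 gives a workable interval rule.
- **That P < 0.05 doubles the error rate, or makes this a superiority trial.** The sentence is general, tied neither to a ratio of 1 nor to a one-sided test. Section 12.1 sets one-sided 2.5%, and a two-sided 0.05 agrees with its 95% interval.
- **That a decision rule would be picked after seeing the event rate.** Section 12.3.2 requires an analysis plan approved before unblinding.

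**Conclusion.** The point holds as a mismatch between two stated parts of the protocol. The margin and sample size rest on an absolute risk difference with a two-sided 95% interval (one-sided 2.5%). The stated primary analysis is a risk ratio with no margin, beside a P-value criterion with no null value.

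If the ratio were judged against the equivalent margin at the planned control risk, power would be about 81% instead of 90%, and 1954 evaluable participants would be needed to restore it. A P < 0.05 test of no difference would not address non-inferiority at all.

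These figures rest on normal approximations with unpooled variances, on 757 evaluable per arm, and on the protocol's 35% and 37%. That the margin is absolute is inferred, because the protocol does not say so, but the exact match to 1514 and 1684 makes the inference secure. The 81% describes what follows if a converted ratio margin is used; the protocol does not say that it will be. The sample size itself is correct.

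**What to change.** In section 12.3.2, add:

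> The primary estimate is the absolute risk difference (relaxed minus tight) in new onset AF; non-inferiority is concluded if the upper limit of its two-sided 95% CI is below 10 percentage points. The risk ratio is supportive for the primary outcome.

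Add this rather than replacing the existing risk-ratio sentence, which also sets the effect measure for in-patient and six-month mortality and should stay for those outcomes.

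Reword the significance sentence to:

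> For superiority-type comparisons, including secondary outcomes, the criterion is two-sided P<0.05.

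In section 12.1, state that the 10% margin and the 2% assumed difference are absolute percentage points.

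The cost is a few sentences in section 12, with matching wording in the analysis plan, to be settled before unblinding. No new data or participants are needed: 1514 evaluable participants still give 90% power, and 1684 to recruit stands.

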## **13. Ethics**

### **13.1. Declaration of Helsinki and Good Clinical Practice**

The study will conform to the spirit and the letter of the declaration of Helsinki, and in accordance with the Barts Health and ICH-GCP. The study will be carried out in accordance with the ethical principles in the Research Governance Framework for Health and Social Care, Second Edition, 2005 and its subsequent amendments as applicable and applicable legal and regulatory requirements.

### **13.2. Ethical committee review**

Health Research Authority (HRA) Research Ethics Committee **TO BE ADDED** have reviewed and approved the trial. The REC number is **TO BE ADDED**. Copies of the letters of approval will be filed in the trial site files at each centre.

### **13.3. Confidentiality Advisory Group**

Written consent will not be available for delegated members of the research team to access hospital notes for patients undergoing CABG surgery to screen them for eligibility. Permission has been granted by the Confidentiality Advisory Group (CAG) to allow notes to be screened and for staff to contact patients prior to a clinic appointment to inform them about the trial. The CAG reference number **TO BE ADDED**.

## **15. Finance and Funding**

This trial is funded by the BHF.

## **16. Indemnity**

### **16.1. Sponsorship**

This trial is sponsored by Barts Health NHS Trust.

### **16.2. Insurance**

All recruiting centres will be covered by NHS indemnity for negligent harm providing researchers hold a contract of employment with the NHS, including honorary contracts held

by academic staff. Medical co-investigators will also be covered by their own medical defence insurance for non-negligent harm.

## **17. Dissemination of Research Findings**

It is our intention to disseminate the results of the trial as widely as possible, including to the patients who participated. This is likely to be through a publication in a peer reviewed journal. Publications will follow the CONSORT guidelines. Authorship will follow international guidelines.

